### Data collection instruments

Community survey and health care provider/stakeholder survey will be done using a structured questionnaire to capture the occurrence of an emergency medical condition in the last 12 months and treatment seeking behaviour, and barriers and facilitators in seeking care. We will also capture the electronic health record data for disease burden, care and outcome related information. Competency of health care providers will be assessed using knowledge and skill observation checklist. Gap analysis of the health facilities will be done using a structured questionnaire which will be developed during formative research based on review of literature and expert consultation.

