### Study design and overview

We plan to conduct a multi-district implementation study using a mixed-methods design that combines formative and evaluation components through three iterative improvement cycles to develop and implement a high-quality emergency care system. Our model will provide quality care to patients with STEMI, stroke, trauma and burns, acute respiratory illness, postpartum haemorrhage and preeclampsia, neonatal emergencies, snake bite and poisoning. The study will be of a three year duration. It will be conducted in collaboration with the state health department.

The study will start with (1) Identification of gaps related to emergency care at pre-hospital, public and private healthcare system; (2) Simultaneously, a community based survey will be done to obtain baseline data on load of EMDs and level of community awareness; (3) Formative research will be done to co-develop a district specific provisional patient centric integrated model of emergency care; (4) optimization of the model through three cycles of iterative processes to provide continuum of care across different levels of the health system; 5. Implementation of the model through hub (tertiary care hospitals) and spokes (a cluster of public health facilities- DH, CHC, PHC) linked via pre-hospital system in a designated geographical area in the district and 6. Evaluation of the model for feasibility, acceptability, cost, effectiveness and coverage in the above five selected districts. It will then be scaled up to the entire district in consultation with the respective state governments and its impact on population coverage will be evaluated (Fig 2). The study results will be disseminated to policy makers at state and national level.

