### Model optimization and development phase

Pilot testing of the model (M0) will be done in a limited sample and geographical setting which is likely to be representative of the entire district in consultation with the state. A single hub and spoke cluster will be chosen to have a representation of each level of health facility (prehospital care, Level 1, Level 2, Level 3, and Level 4) for each of the emergency conditions. Pre- and post-implementation data will be analysed to assess acceptability, feasibility and effectiveness based on process and quality outcome measures. Quantitative data on key indicators on the implementation strategy (e.g., effectiveness of training of care providers, appropriateness and effectiveness of educational materials), process indicators (e.g., adherence to new care protocols, patient satisfaction), and implementation measures (e.g., acceptability by the care providers) will be collected. The model will be refined based on a review of the provisional model, data collection and evaluation of the key indicators. As described in the formative research multi-stakeholder consultation (Co-design workshop), in-depth interviews and focus group discussions will be done to get further insights. Key areas will be identified where the provisional model has not worked effectively. Necessary adjustments will be made to the model in a consultative manner. Subsequent cycles will be developed by re-iterating the same process. A total of 3 iterative processes will be done to refine the model and to develop the final model (Px) (Fig 4). Each disease process will be deployed sequentially, and iterative processes and periods will be conducted accordingly. The threshold for initiating the scale-up phase will be decided during the formative research phase after the baseline surveys and mapping by the research team. The threshold will be multidimensional and the irrespective of attaining the threshold after 3 iterative cycles scale up will be initiated.

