### Scaling up of the final model

The piloted final model ‘Px’ will be scaled up step-wise to the entire district in a phased manner. The scaling-up sequence will start from the hub and spoke system where pilot testing was conducted and then progressively moved to the other spokes and other hubs of the district. A detailed scale-up strategy, tools to be used for scale-up and scalability of the model will be co-developed by consultation with the state. The objective during this phase is to implement the final high-quality integrated INDIA-EMS model across the whole district to achieve 80% population coverage of this model. This rollout will be done primarily by the district administration (the implementation team), with support from the program learning team. The outcome assessment team will conduct the concurrent evaluation and the endline population survey.

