Evaluation will be done at baseline, concurrently during the implementation of the model and at the endline(S5 Table). Baseline, concurrent evaluations, and end-line survey data will be analysed to assess the feasibility, acceptability and the cost of the implementation of the model, and the effectiveness of the implemented model in terms of emergency care preparedness and coverage. Concurrent evaluation: Health facility assessment, qualitative interview with stakeholders, competency assessment of care providers will be done concurrently at an interval of three months. Post-care interviews (telephonically) of patients will be done to assess coverage and timeliness of care, expenditure, pathway of care, and delay in care. Endline evaluation: Endline survey will be conducted after the completion of the implementation phase. The sampling strategy and methodology of the endline survey will be similar to the baseline survey. Objective of the endline survey will be to estimate the increase in population coverage and health facility preparedness as compared to the baseline. The estimate of population coverage (i.e., reaching the appropriate health facility within a specified time frame as per the condition; this time frame will be decided during the formative research) obtained during the baseline survey will be used to calculate the sample size for the endline survey. Thus, the sample size for the endline survey will be calculated after the analysis of the results of the baseline survey. We are providing an illustration for sample size required for different scenarios of population coverage assuming a power of 80%, the confidence level of 95%, and a non-response rate of 20%. Thus, sample size included in baseline survey (at the district level) will be sufficient if there is at least 20% increase in population coverage from pre-intervention to post-intervention.

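### Nothing separates the endline survey's 12-month recall from the phased roll-out, so any area active for under 12 months at interview dilutes the coverage gain

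*Protocol article*

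**What the plan says.** All places are in the protocol article.

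- **Recall.** Data collection instruments: the community survey is to "capture the occurrence of an emergency medical condition in the last 12 months".
- **Endline method and timing.** The evaluation paragraph that closes Secondary outcomes: "The sampling strategy and methodology of the endline survey will be similar to the baseline survey", and "Endline survey will be conducted after the completion of the implementation phase". No interval is given.
- **Roll-out.** Scaling up of the final model: the model "will be scaled up step-wise to the entire district in a phased manner", and "The scaling-up sequence will start from the hub and spoke system where pilot testing was conducted", moving on to other spokes and hubs. Activation dates therefore differ between areas of one district.
- **Purpose.** The same evaluation paragraph: "Objective of the endline survey will be to estimate the increase in population coverage and health facility preparedness as compared to the baseline". Coverage is the primary outcome indicator, and 80% population coverage is the study's aim.
- **Analysis.** Quantitative analysis names repeated-measures ANOVA, mixed models, GEE, ARIMA and Cox regression. It mentions neither local activation date nor classification of events by exposure.

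**The concern.** A 12-month look-back measures post-implementation coverage only if the model was already running where and when each reported emergency happened. With phased activation, the areas reached last have the shortest exposed period before interview. Followed as written, an emergency that occurred before the local spoke was active enters the endline estimate as a post-implementation event.

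Such events carry roughly baseline coverage, so they pull the endline estimate toward baseline. The stake is the primary indicator: a model that works could appear to give a smaller increase, or to miss 80%, because of the calendar alone. Facility preparedness is assessed at the facilities and does not rest on this recall, so the point concerns coverage only.

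It is not a detail that can safely wait for analysis. If the month of an event is not asked at interview, it may not be recoverable afterwards.

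**Working it through.** **Step 1: reproduce the plan's figures.** Inputs from the evaluation paragraph: power 80%, confidence level 95%. For two independent proportions with unpooled variance and continuity correction:

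n0 = (1.960 + 0.842)² × [p1(1−p1) + p2(1−p2)] / (p2−p1)²

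n = (n0/4) × [1 + √(1 + 4/(n0 × |p2−p1|))]², rounded up

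- 20% to 40%: n0 = 7.849 × 0.40/0.04 = 78.5, n = 88.2, so 89.
- 20% to 30%: n0 = 7.849 × 0.37/0.01 = 290.4, n = 310.1, so 311.

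All 13 case numbers in Table 2 are reproduced exactly in this way.

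**Step 2: unexposed share of recalled events.** The documents give neither the roll-out length R nor the gap g between the last activation and the interview (both in months), so a range is shown. Assume events spread evenly over the 12 months and activation dates spread evenly over R months ending g months before interview. An area active for a months has max(0, 12−a) unexposed months, with a uniform from g to g+R. The mean unexposed share s is:

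- g + R ≤ 12: s = 1 − (g + R/2)/12
- g < 12 < g + R: s = (12−g)²/(24R)
- g ≥ 12: s = 0

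| R | g = 0 | g = 3 | g = 6 | g = 12 |
|---|---|---|---|---|
| 3 | 87.5% | 62.5% | 37.5% | 0 |
| 6 | 75% | 50% | 25% | 0 |
| 12 | 50% | 28% | 12.5% | 0 |
| 24 | 25% | 14% | 6% | 0 |

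With g = 0 and R up to 12, R/24 is the exposed share, not the unexposed one. For a fixed gap, a longer roll-out gives less dilution, because more areas were activated early.

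**Step 3: effect on the estimate.** Observed endline coverage = p1 + (1−s)(p2−p1), taking unexposed events to have baseline coverage.

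- s = 50%: a true 20% to 40% is seen as 20% to 30%. Table 2 needs 311 cases instead of 89, and 23,383 people instead of 6,692.
- s = 50%: a true 40% to 60% is seen as 40% to 50%. Table 2 needs 405 cases instead of 104, and 30,451 people instead of 7,820.
- A true 40% to 80% is seen as 75%, 70% or 60% at s = 12.5%, 25% or 50%.

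**Step 4: power with 89 cases per survey, true 20% to 40%.** Power = Φ[(d − 1/89)/SE − 1.96], where d is the observed difference and SE = √{[p1(1−p1) + p2(1−p2)]/89}, with p2 the observed endline coverage.

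| s | Observed endline | Power |
|---|---|---|
| 0 | 40% | 0.80 |
| 12.5% | 37.5% | 0.69 |
| 25% | 35% | 0.56 |
| 50% | 30% | 0.28 |

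**Step 5: cost of counting only exposed events.** The contrast returns to 20% to 40%, but the endline must yield 89/(1−s) reported cases to keep 89 exposed ones: 102, 119 and 178 at s = 12.5%, 25% and 50%. Scaling Table 2's population figure likewise gives 6,692/(1−s): about 7,648, 8,923 and 13,384 people.

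**The case against.** The strongest reply is that the article does not say when the endline takes place beyond its following completion. The evaluation schedule is referred to S5 Table and the overview to Fig 2, neither of which is shown, and the detailed scale-up strategy is still to be developed with the states. Progress of the study runs from January 2024 to December 2027, about 48 months, so a clear gap is possible. Event-level eligibility and questionnaire fields may also sit in documents not at hand. This stands, and it makes the point conditional. It does not remove it: "The study will be of a three year duration", and formative work, baseline survey, three optimisation cycles, district scale-up and endline must all fit. Even the longer calendar guarantees no gap.

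A reader might infer more than the text supports:

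- **That the endline follows immediately, so dilution is certain.** The text gives an order, not an interval.
- **That conditions are also phased during scale-up.** "Each disease process will be deployed sequentially" describes the pilot optimisation cycles. The scale-up section describes phasing by area only, and that is enough for the argument.
- **That the plan rests on a before-after contrast alone.** Concurrent evaluations, including telephone interviews on coverage and timeliness, also feed the assessment, and Geo spatial analysis plans filtering by place and time. None of these sorts endline survey events by local activation, and the increase over baseline is assigned to the endline survey.
- **That the recall window explains the lack of a control group.** Secular change is a separate matter and can bias either way. Dilution acts only toward no change.

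**Conclusion.** The point holds in conditional form. The article combines a 12-month recall, an area-by-area roll-out and an endline tied only to completion of implementation, with no minimum interval and no exposure rule. If any area has been active for under 12 months at interview, the coverage increase and the 80% attainment are biased toward no change. If all have been active for 12 months or more, the bias is zero.

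The size cannot be settled from the document. Over the ranges tried with g under 12 months, the unexposed share runs from 6% to 87.5%. The 50% case (R = 12, g = 0) is an illustration, not an estimate. The figures assume events and activations spread evenly in time, recall equally complete across the 12 months, and baseline-level coverage before activation. Better recall of recent events would lower s. So would an early-activated pilot cluster that holds a large part of the district's population, a share the document does not give.

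The point is worth acting on because it touches the primary indicator. It also bears on the claim that the baseline survey size suffices for an increase of at least 20%: that reasoning takes the full increase to be visible at endline.

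**What to change.** - Ask the month of each reported emergency. Keep a log of the activation date of the hub and spoke serving each sampled PSU, by condition too if conditions are phased during scale-up.
- Define the primary endline set as events after local activation, and report the all-events comparison as a sensitivity analysis. Alternatively, time the endline so that the whole recall window falls after the last activation.
- When the endline size is calculated after baseline, as already planned, base it on the expected number of exposed events and restate the detectable difference on that number.
- Treat any use of pre-activation events as same-period comparators as exploratory: the roll-out order is not randomised and the numbers will be small.

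The data cost is one question and one log. The real cost is the loss of a share s of endline events, which means either a larger survey (Step 5) or a larger detectable difference. Delaying the endline avoids that loss but takes calendar time.

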### Data management

Data management will involve the use of a paperless data collection tool and will include geo-spatial tagging and analysis (using space-time matrix and kernel density), development of a Health Management Information System (HMIS) which includes registers, reports, and databases, real-time supportive supervision, interim analysis for process indicators through serial analysis, internal checks for data validation, text mining for qualitative data, and an iterative “inductive” framework analysis. The digital tools and the platform will be developed along with the ICMR HQ and the Gujarat team. The data servers and management will be hosted at ICMR. The qualitative data from FDG, IDI’s and semi-structured interviews will be transcribed and translated at the study site and analysed. The quantitative data management will be done at the respective study site.

### Progress of the study

The study began on 12 January 2024 in all study sites. The participant recruitment is estimated to be completed by December 31, 2027, followed by data analysis and publication of results by February 2028.

### Data analysis plan

The collected data will be analyzed using both quantitative and qualitative methods

#### Qualitative analysis.

We propose to adapt grounded theory in this research looking at the nature of inquiry. We will start with open coding and try to identify concepts in the data without predetermined categories. Through constant comparison, codes will be refined, and will be converted into categories. All the categories will be leading to the development of a theoretical framework. As this phenomenon is also nearer to applied policy research, we further propose to do a framework analysis where we will use a matrix to organize and interpret data by themes and categories. After the thematic analysis, we will adapt a semi-quantitative text mining approach where we will be converting text to a tokenized data frame and stop -words will be anti-joined to this date frame. The word frequencies will be plotted using bar graph and by word cloud diagram. Finally, we will explore the correlation between words and a network plot of the same will be plotted

#### Quantitative analysis.

The data will be duly checked for duplication, redundancies, missing values, and outliers. The key variables will be identified and summarized by measure of central tendency and measure of dispersion as per variable type. The incidence of emergency medical conditions will be calculated separately for urban and rural areas and pooled weighted estimates will be calculated based on distribution of population in urban and rural areas. The effect of the implementation model will be assessed statistically using appropriate methods as described here; We will perform the repeated measure Analysis of variance (ANOVA) as a univariate analysis for those dependent variables which are continuous in nature and having a within-subject correlation. The multivariate analysis for the same variables will be performed by linear mixed effect models (to account for population level and individual level variability). We further propose to calculate a population-average effect by Generalized Estimating Equations (GEE) looking at the structure of the data collection plan and robustness of GEE in the case of model misspecification. The temporal pattern (if any) in some variables will be checked by autoregressive integrated moving average (ARIMA) and if any temporal pattern is indicated we will perform a time-to-event analysis using Cox proportional hazard model.

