Though integrated emergency care systems are considered a solution for providing accessibility to emergency care in diverse geographical settings, evidence based information for planning and implementing a patient centric integrated emergency care system, particularly in low resource settings, is required. Therefore, in the initial phase of the study we plan to conduct:(i) a systematic literature review: to synthesise evidence for an integrated emergency care system, which has been adopted globally or within India to meet the needs of the population served. This will provide an overview of what has been tried to be integrated and its purpose; how this can be used to develop the model, processes, strategies and structure within the context of the needs of the population of selected districts. (ii) health system readiness: a. health facility and pre-hospital (ambulance and helpline centres) resource and infrastructure assessment in the study district and a defined area in adjoining districts; b. Mapping of emergency care system: geo spatial mapping of facilities; mapping of current emergency care pathways, care processes and referral pathways using observation checklists, direct observation, and interview with health care providers; c. competency assessment of care providers and 1^st^ responders to assess the knowledge and skills of healthcare providers; d. budgetary provisions abstracted from administrative data including public and private insurance systems and; e. indicators of the current state of emergency care, e.g., hospital emergency visits, types of emergencies, patient outcomes.(iii) A community-based household survey: to estimate the burden of EMDs in the community and assess the health care services sought after the event. The survey data will provide information on the proportion who sought care, pathway of care & referral pathway, delay in seeking care, the expenditure incurred during care provision for the emergency medical condition and utilisation of insurance services. A multistage sampling strategy will be adopted. The study population will be stratified into urban and rural areas. Villages will be the primary sampling unit (PSU) in rural areas. Villages with a population of less than 500 will be excluded from the sampling frame, and villages with a population of more than 5000 will be split into clusters to have an approximate population of around 2000 in each cluster. In an urban area, census enumeration blocks will be a PSU. Sample size is calculated to estimate the burden of emergency medical conditions. Considering the burden of emergency conditions as 141/10000 population (Table 2), assuming a confidence level of 95% and a relative precision of 25% and design effect of one (design effect is considered as one as due to rarity of outcome the events are less likely to be clustered), the required sample size is 4292. Considering a non-response rate of 20% the sample size comes out to be 5365 which is further rounded off to 6000. A total of 60 PSUs will be randomly selected (PSU stratification for urban and rural will be based on district’s urban:rural distribution) and 100 households will be randomly selected from each PSU. All the individuals in the selected household will be included for the purpose of data collection.

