#### Primary outcomes.

The primary outcome indicator is coverage (S3 Table), i.e., the proportion of patients who were provided definitive care for the specified emergency medical condition at an appropriate health facility in a time-sensitive manner. The appropriate facility will be defined during the facility mapping for each emergency condition. Time sensitivity will be defined as per disease condition and decided based on expert consultation and available evidence during the formative phase.

I. *Emergency health care coverage indicators that would be covered are:*a) Proportion of patients who sought care for any emergency medical conditionb) Proportion of patients who used ambulance services to reach health facility for a emergency medical conditionc) Proportion of times an ambulance responded to the emergency calls.d) Proportion of patients who were provided definitive care for the specified emergency medical conditione) Proportion of patients who utilized PMJAY/state government insurance schemes during care for emergency medical conditionsf) Proportion of patients who had catastrophic expenditure during care for emergency medical conditions

The coverage indicator will be disaggregated for different emergency conditions

The second indicator which will be assessed is preparedness of the emergency health care.

II. *Emergency health care preparedness indicators*a) Proportion of health facilities having a fully equipped functional ambulanceb) Proportion of ambulance personnel trained in “at scene and transit” management of common emergenciesc) Proportion of lay first responders trained in “at scene” management of common emergenciesd) Proportion of health facilities having round-the-clock availability of complete emergency care team trained in management of medical emergencies/trauma/poisoninge) Percentage health facilities having availability of key/essential equipment and medications required to provide definitive care for specified emergency conditionf) Percentage health facilities having an infrastructure readiness score above a desirable levelg) Proportion of health facilities providing care as per Standard Treatment Workflow (STW) and Standard Operating Procedure (SOP) as per the level of care for the management of emergency medical conditionh) Proportion of health facilities conducting regular mortality audits of emergency medical conditioni) Proportion of health facilities utilizing RKS funds for emergency care

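### The rule that a temporal pattern found by ARIMA leads to a Cox model is invalid, and GEE is the only named effect method that can fit coverage

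*Protocol article*

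**What the plan says.** All references are to the protocol article.

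- **Primary outcomes.** Coverage is "the proportion of patients who were provided definitive care for the specified emergency medical condition at an appropriate health facility in a time-sensitive manner". Six coverage and nine preparedness indicators follow, all of them proportions or percentages.
- **Evaluation text under Secondary outcomes.** "Objective of the endline survey will be to estimate the increase in population coverage and health facility preparedness as compared to the baseline". On sampling: "The sampling strategy and methodology of the endline survey will be similar to the baseline survey". Facility assessments are repeated every three months during implementation.
- **Formative research.** Each district selects 60 PSUs at random, and "100 households will be randomly selected from each PSU".
- **Data collection instruments.** The survey is "to capture the occurrence of an emergency medical condition in the last 12 months and treatment seeking behaviour".
- **Quantitative analysis.** The effect of the model is to be assessed by "repeated measure Analysis of variance (ANOVA) as a univariate analysis for those dependent variables which are continuous in nature" and correlated within subject, by linear mixed models for those same variables, and by GEE for a population-average effect. ARIMA then checks some variables, not named, and "if any temporal pattern is indicated we will perform a time-to-event analysis using Cox proportional hazard model".
- **Scaling up of the final model.** The final model "will be scaled up step-wise to the entire district in a phased manner", starting from the pilot hub and its spokes.

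**The concern.** The ARIMA-to-Cox sentence is a decision rule that the article states. It is not a detail left for later, and an analysis plan that follows the article would inherit it. It is also the only response to a temporal pattern that the effect analysis names, and it does not answer the question that such a pattern raises: how much of a change would have happened anyway.

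That question matters because the article describes no control district and the five districts were chosen purposively. An analyst who found a trend in an indicator and followed the rule would change the type of outcome being analysed and would not adjust for the trend. The section also does not say which of its listed methods is meant for coverage, although only one of them can serve.

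**Working it through.** **1. What the primary comparison is.** Table 2 gives the number of emergency cases needed for a given rise in coverage. Its figures reproduce as a comparison of two independent proportions with unpooled variance and a continuity term, at two-sided 5% and 80% power:

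n = (1.960 + 0.842)² × [p₁(1−p₁) + p₂(1−p₂)] / d² + 2/d, where d = p₂ − p₁

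- 30% to 50%: 90.3 + 10 = 100.3 (stated 101)
- 10% to 20%: 196.2 + 20 = 216.2 (stated 216)
- 30% to 40%: 353.2 + 20 = 373.2 (stated 373)
- 40% to 80%: 19.6 + 5 = 24.6 (stated 25)

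All 13 case numbers agree within one case. So the study is sized for a binary outcome in two independent groups of cases.

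**2. Which named method can fit that.**

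- Repeated-measures ANOVA: limited by the plan to continuous variables with within-subject correlation, so not coverage.
- Linear mixed model: for the same variables, so not coverage.
- GEE: with a binomial family and PSU as the cluster it fits coverage. The article does not tie it to that outcome.
- ARIMA: needs a long regular series. The two surveys give 2 points. Quarterly assessments give 36/3 = 12 points over the stated three years, or 48/3 = 16 on the January 2024 to December 2027 dates under Progress of the study.
- Cox: needs individual event times. Coverage, as a yes/no proportion from two surveys, supplies none. Time to arrival and time to treatment, listed as process indicators, do.

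**3. Whether the rule deals with trend.** A Cox model can carry calendar time as a covariate, but the plan states no such term. As written, a finding of trend changes the model class and leaves the trend where it was.

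**4. What trend can do to the coverage comparison.** With two rounds, survey round and calendar time are the same contrast. A background rise of s points per year adds s × (years between surveys) to the estimate. The documents give no s, and they give no survey dates. Assuming s = 3:

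- 2 years apart: 6 points
- 3 years apart: 9 points, or 9/20 = 45% of the 20-point increase for which the evaluation text calls the survey size sufficient

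**5. Chance of a significant result from trend alone.** Assume 30% baseline coverage, no effect of the model and no clustering. The probability of a significant rise is Φ[(d − 1.96·SE₀)/SE₁], with SE₀ from the pooled proportion and SE₁ from the two separate ones. For 101 cases per survey and d = 0.10, SE₀ = 0.0671 and SE₁ = 0.0667, which gives Φ(−0.47) = 0.32.

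| Background rise | 101 cases per survey | 373 cases per survey |
|---|---|---|
| 5 points | 0.11 | 0.31 |
| 10 points | 0.32 | 0.82 |
| 15 points | 0.60 | 0.99 |

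The nominal two-sided rate is 0.05. The sizes of rise are illustrations, not estimates.

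**The case against.** The strongest reply is that only one sentence is at fault, and that it concerns unnamed variables. Much of that reply stands, and it rules out several stronger readings.

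- *That the stated analyses do not fit the primary outcome at all.* A reader might infer this from the prominence of ANOVA and mixed models. The article never assigns them to coverage, and GEE is named. Link, cluster unit and covariates are details that an article commonly leaves to the full plan. Continuous repeated measures for ANOVA or mixed models may exist, such as provider competency or the infrastructure readiness score.
- *That the ARIMA-to-Cox rule is why secular trend stays in the coverage estimate.* It is not. The uncontrolled before-after design is the cause, and a GEE with survey round as the effect carries the same bias.
- *That ARIMA is impossible here because there are at most 12 points.* That ceiling holds for the quarterly assessments. Data collection instruments and Data management also plan electronic health records and an information system, which could give denser series.
- *That the plan states fresh, independent samples.* It says only that the sampling will be similar. Independence is a fair inference from the random household selection and from Table 2, and re-use of the same PSUs is left open.
- *That Cox has no place.* Time to arrival and time to treatment are legitimate uses. Only the trigger is wrong.

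The reply does not rescue the rule itself. No choice of variable makes a pattern in an ARIMA fit a reason for a hazard model.

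**Conclusion.** The ARIMA-to-Cox rule is wrong as written and should go. This conclusion rests on the text alone and on no assumed figure. GEE is the one listed effect method that can analyse coverage, and the plan should say that it is the one meant.

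For coverage there is a limit that no change of model removes: the two-survey difference is an uncontrolled before-after change. How much secular trend adds is unknown. The 6 to 9 points above rest on an assumed 3 points per year over 2 to 3 years. The rejection probabilities rest on an assumed 30% baseline, zero effect and no clustering. No stated sample size has to change on account of this point.

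**What to change.** 1. Delete the rule that leads from ARIMA to Cox.
2. For the quarterly facility indicators, use a binomial GEE or GLMM with a term for calendar quarter and an indicator that switches on at go-live. Define go-live by facility and, because Model optimization and development phase deploys conditions sequentially, by condition where needed. Facilities not yet reached then serve as a concurrent comparison. State that the roll-out order is not random, since it spreads from the pilot hub.
3. Use Cox only for defined times, such as time to arrival or time to treatment, whatever ARIMA shows.
4. For coverage, tie the GEE already named to the binary outcome, with survey round as the effect and standard errors clustered on PSU. Report the result as an uncontrolled before-after change and say that secular trend cannot be separated from it.
5. Keep ANOVA and the linear mixed model for named continuous repeated measures.

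The cost is analysis wording and code, plus a log of go-live dates. Phased scale-up and quarterly assessments are already planned. The dates are easiest to record as they occur, so the log should begin before scale-up.
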